### Recruitment and Sampling Strategy

The participant selection sampling strategy was a convenient approach based on the availability and willingness to participate of the patients who fulfilled the study criteria [21].

Participating centers were selected based on geographic distribution and availability of primary health care teams. Teams received virtual training sessions. Sessions included information related to the background, objectives, protocol procedures, and data collection methods before participant recruitment. The study recruitment period lasted 6 months.

### Study Procedures and Timeline

Potential participants were identified by local study physicians and nurses using the primary care eCAP (Catalan Health Institute) electronic clinical record software. Each participant underwent 4 study visits. Initially, a preselection visit was conducted through electronic health record review without direct patient contact. Eligible individuals were then contacted and provided with detailed study information. Those who agreed to participate were invited to the inclusion visit (visit 0), during which written informed consent was obtained by research staff. This visit involved a clinical interview, a physical examination, laboratory testing (including C-peptide and GADAb measurements), and the placement of a CGM device. All participants used CGM for 10 to 15 days prior to the intervention. Two weeks later, the first follow-up visit (visit 1) was conducted. At this visit, therapeutic decisions were made based on C-peptide and GADAb results, and treatment was adjusted according to the predefined therapeutic intervention algorithm (Figure 1).

**Figure 1. F1:**
[figure not shown]
Therapeutic intervention algorithm. CGM: continuous glucose monitoring; GADAb: glutamic acid decarboxylase autoantibody; GLP-1: glucagonlike peptide-1; SGLT2: sodium-glucose cotransporter type 2.

The second follow-up and final in-person study visit (visit 2) took place at month 6, during which outcomes were assessed. Glycemic control was evaluated through hemoglobin A_1c_ (HbA_1c_) testing, and other clinically relevant follow-up variables were collected. Throughout the study period, participants received additional follow-up and support as needed via telephone or virtual consultations from their primary health care team.

Figure 2 illustrates the planned participant flow and study procedures across the different study visits.

**Figure 2. F2:**
[figure not shown]
Study flowchart. eCAP: electronic clinical record software of primary care (Catalonia); MDI: multiple daily insulin injection; T2DM: type 2 diabetes mellitus.

### Data Collection and Management

#### Overview

Data for this study are collected from electronic medical records and patient-reported questionnaires during study visits. Clinical and demographic information, including age, sex, educational level, BMI, diabetes duration, comorbidities, complications, and current pharmacological treatment, is obtained from the eCAP (electronic medical record) software and supplemented by medical interviews. Laboratory variables, including C-peptide, GADAb, HbA_1c_, and estimated glomerular filtration rate, are extracted from recent laboratory reports or requested when unavailable. CGM data, including metrics such as time in range, hypoglycemia episodes, and glucose variability, are downloaded directly from the devices used by participants throughout the study. Patient-reported outcomes, including quality of life, treatment satisfaction, medication adherence, and physical activity, are assessed using validated questionnaires. All study variables and corresponding time points are summarized in Table 1. In addition, detailed information on the study variables, including their definitions and data sources, is provided in Multimedia Appendix 2.

**Table 1. T1:** Study timeline, variables, and procedures.

Data collected	Evaluation time point			
	Preselection	Visit 0—inclusion	Visit 1—intervention (2 weeks)	Visit 2—final follow-up (6 months)
Inclusion and exclusion criteria	✓	✓		
Sociodemographic data^a^		✓		
Anthropometric data^b^		✓		✓
Clinical data^c^		✓		✓
CGM^d^ data			✓	✓
Laboratory data^e^		✓		✓
Smoking status		✓		
Pharmacological treatment^f^		✓		✓
Severe hypoglycemia^g^		✓		✓
Questionnaires^h^		✓		✓

a Age, gender, primary care center, current occupational status, level of education, number of children, date of menopause, and whether the participant is the sole caregiver of another person.

b Weight, height, BMI, and abdominal circumference.

c Arterial hypertension, dyslipidemia, micro- and macrovascular complications, heart failure, and renal disease of any etiology (estimated glomerular filtration rate <60 mL per minute per 1.73 m2).

d CGM: continuous glucose monitoring.

e Inclusion visit: hemoglobin A_1c_ (HbA_1c_), glutamic acid decarboxylase autoantibody, glycemia, and C-peptide; final visit: HbA_1c_.

f Prescription and dosage of diabetes drugs.

g Inclusion visit: last 12 months; final visit: 6 months of study.

h International Physical Activity Questionnaire, Diabetes Treatment Satisfaction Questionnaire–Status Version, Diabetes Treatment Satisfaction Questionnaire–Change Version (final visit only), Adherence to Refills and Medications Scale–Spanish Version, and Spanish version of the Diabetes Quality of Life Questionnaire.

All data are systematically recorded using an electronic case report form (eCRF) specifically developed for this study. Local investigators at each participating center are responsible for ensuring accurate, complete, and timely entry of study data into the eCRF. We perform quality control procedures to verify informed consent and participant eligibility prior to data entry. In addition, the coordinating research team regularly monitors the eCRF data entries to ensure high data quality and compliance with good clinical practice standards throughout the study.

#### Questionnaires

Several validated questionnaires are used to assess patient-reported outcomes related to quality of life, treatment satisfaction, medication adherence, and physical activity. These questionnaires are administered at both the baseline and final study visits (6 months), as outlined in the study timeline (Table 1).

A detailed description of each questionnaire, including constructs assessed, number of items, scoring, and references, is provided in Table 2.

**Table 2. T2:** Summary of patient-reported outcome questionnaires used in this study.

Questionnaire	Construct measured	Description and domains	Number of items	Response scale	Scoring and interpretation	Time points	Reference
ESDQoL^a^	Diabetes-related quality of life	Assesses multiple domains of diabetes-specific quality of life, with domain impact weighted by patient-reported importance	43	5-point Likert scale	Weighted average score; higher scores indicate poorer quality of life	Baseline and 6 months	[22]
DTSQs^b^	Diabetes treatment satisfaction	Measures satisfaction with current diabetes treatment; includes separate items on perceived frequency of hyperglycemia and hypoglycemia	8	7-point Likert scale (0 to 6)	Sum of 6 items (range 0 to 36); higher scores indicate greater satisfaction; 2 items analyzed separately	Baseline and 6 months	[23]
DTSQc^c^	Change in treatment satisfaction	Assesses perceived change in satisfaction compared with previous treatment	8	7-point Likert scale (–3 to +3)	Positive scores indicate improvement; negative scores indicate deterioration	6 months	[23]
ARMS-e^d^	Medication adherence	Evaluates adherence behaviors and barriers related to medication use	12	4-point Likert scale (“never” to “always”)	Lower total scores indicate better adherence	Baseline and 6 months	[24]
IPAQ^e^	Physical activity	Assesses physical activity in the previous 7 days, including walking, moderate and vigorous activity, and sedentary behavior	7	Frequency (d per wk) and duration (min per d)	Physical activity expressed as MET^f^ min per week; higher values indicate higher activity levels	Baseline and 6 months	[25]

a ESDQoL: Spanish Diabetes Quality of Life Questionnaire.

b DTSQs: Diabetes Treatment Satisfaction Questionnaire–Status Version.

c DTSQc: Diabetes Treatment Satisfaction Questionnaire–Change Version.

d ARMS-e: Adherence to Refills and Medications Scale–Spanish Version.

e IPAQ: International Physical Activity Questionnaire–Short Form (Spanish version).

f MET: metabolic equivalent of task.

### Intervention Algorithm

Therapeutic decisions in the study are guided by an algorithm based on C-peptide and GADAb levels (Figure 1). Patients with a C-peptide level below 0.3 nmol/L and positive GADAb are considered suspected type 1 diabetes cases; they continue MDI and CGM and are referred for specialized care. Those with similarly low C-peptide levels but negative GADAb also continue MDI and CGM with no changes in treatment.

For patients with intermediate C-peptide values (0.3‐0.7 nmol/L), the approach varies based on GADAb status. If GADAb is positive, treatment remains unchanged with continued MDI and CGM. However, if GADAb is negative, clinicians consider discontinuing prandial insulin and introducing noninsulin hypoglycemic agents as appropriate.

Participants with C-peptide levels above 0.7 nmol/L regardless of GADAb status are also considered for discontinuation of prandial insulin and initiation of noninsulin therapies. In individuals who discontinue prandial insulin, CGM use is typically discontinued as well as they do not meet the criteria for public funding [26].

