### Study Outcomes

We defined the primary study outcome as the proportion of participants in whom prandial insulin is successfully discontinued after the application of the therapeutic algorithm and who remain without prandial insulin at the final visit (6 months).

Secondary outcomes encompass several domains. Glycemic control following therapeutic optimization is evaluated through changes in HbA_1c_ and CGM-derived metrics, including time in range and time below range. Patient-reported outcomes are also assessed by comparing changes from baseline to 6 months after the intervention, including changes in quality of life (using the Diabetes Quality of Life Questionnaire), treatment satisfaction (using the Diabetes Treatment Satisfaction Questionnaire, both status and change versions), medication adherence (measured using the Adherence to Refills and Medications Scale), and physical activity levels (evaluated using the Spanish version of the International Physical Activity Questionnaire).

Safety outcomes include the number of severe hypoglycemic episodes at the final visit 6 months after the intervention compared with the 12-month period before enrollment. The study also examines the predictive value of CGM metrics by analyzing their association with pancreatic reserve and insulin resistance considering both continuous and categorical variables.

Finally, among patients who continue prandial insulin and CGM use for 6 months, the study assesses the impact of CGM on glycemic control (HbA_1c_ and CGM metrics), as well as changes in quality of life, treatment satisfaction, and medication adherence.

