CGM variables will also be examined as potential predictors of pancreatic reserve and insulin resistance. Depending on whether outcomes are continuous or categorical, linear or logistic regression models will be applied. Results will be expressed as regression coefficients or odds ratios with corresponding 95% CIs.

Loss to follow-up will be quantified and reported as the proportion of participants without outcome data at each follow-up time point. When available, reasons for loss to follow-up will be documented. Baseline characteristics of participants with complete follow-up and those lost to follow-up will be compared to assess potential differential attrition. A complete-case analysis will be used as the primary analytical approach when the proportion of missing data is low, and missingness will be considered compatible with a missing completely at random mechanism. To account for potentially informative missingness, multiple imputation by chained equations will be performed under a missing-at-random assumption, including all variables used in the main analyses and auxiliary variables related to missingness.

All statistical analyses will be performed using the R software (version 4.1.2; R Foundation for Statistical Computing), with a 2-sided *P* value of <.05 considered statistically significant.

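### Participants who stop prandial insulin typically also stop CGM, yet 6-month CGM change, group comparison and imputation are planned with no exception for them

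*Protocol article*

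**What the plan says.** - **Before the intervention, everyone has CGM.** Study Procedures and Timeline: "All participants used CGM for 10 to 15 days prior to the intervention".
- **After prandial insulin is stopped, CGM usually ends.** Intervention Algorithm: "In individuals who discontinue prandial insulin, CGM use is typically discontinued as well as they do not meet the criteria for public funding".
- **CGM is nevertheless scheduled at month 6 without restriction.** The Overview under Data Collection and Management says "All study variables and corresponding time points are summarized in Table 1", and that table ticks CGM data at Visit 1 and Visit 2. Its footnotes qualify the laboratory and severe hypoglycaemia rows by visit. The CGM footnote only spells out the abbreviation.
- **The data source is the participant's own device.** The same Overview says that CGM data "are downloaded directly from the devices used by participants throughout the study".
- **CGM change is a secondary outcome, not limited to any group.** Study Outcomes: "Glycemic control following therapeutic optimization is evaluated through changes in HbA_1c_ and CGM-derived metrics, including time in range and time below range". A separate, later analysis is limited: "among patients who continue prandial insulin and CGM use for 6 months, the study assesses the impact of CGM on glycemic control".
- **The analysis text is general.** Sample Size and Statistical Analysis lists CGM metrics among the secondary outcomes. It then plans paired tests over time, comparisons of discontinuation with continuation, and mixed models. For missing data it allows complete cases when missingness is low and compatible with missing completely at random (MCAR). It adds that "multiple imputation by chained equations will be performed under a missing-at-random assumption, including all variables used in the main analyses". CGM is not exempted from any of this.

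**The concern.** The treatment decision at Visit 1 largely determines who has CGM data at Visit 2. The participants whose regimen the algorithm is meant to simplify are the ones who usually lose the sensor. Three planned analyses are affected:

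1. A pooled before-after change in time in range or time below range would rest mostly on participants kept on prandial insulin, yet be presented as glycaemic control after therapeutic optimization.
2. A discontinuation-versus-continuation comparison of CGM metrics would have very few observations on one side.
3. Chained-equations imputation would fill in discontinuers' 6-month CGM values largely from relationships seen in people on a different regimen.

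This matters because the study's hypothesis is that prandial insulin can be stopped safely. Time below range and time in range are metrics a reader would look to for that.

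**Working it through.** **Inputs from the protocol** (Sample Size and Statistical Analysis): source population 1388, expected proportion 25%, margin of error 5 percentage points, 95% confidence, sample size 239.

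**Step 1: reproduce the stated sample size.** Without a finite population correction, n0 = 1.96² × 0.25 × 0.75 / 0.05² = 288.1. With the correction, n = 288.1 / (1 + 287.1/1388) = 238.7, rounded up to 239. The stated figure reproduces, so the sample size is not at fault.

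**Step 2: expected group sizes.** 239 × 0.25 = 59.75, about 60 discontinuers, leaving about 179 continuers.

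**Step 3: discontinuers with paired CGM.** The protocol puts no number on how often CGM stops, so the share is an assumption, varied from 70% to 100%. All continuers are taken to have month-6 CGM. Observed discontinuers = 59.75 × (1 − share stopping). The last two columns give the standardised difference detectable with 80% power at two-sided 0.05, by normal approximation:
- between groups: (1.96 + 0.84) × √(1/n₁ + 1/n₂), with n₂ = 179.25;
- paired change in discontinuers: (1.96 + 0.84) / √n₁.

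| Share of discontinuers stopping CGM | Discontinuers with pairs | Cohort missing | Pooled pairs from continuers | Detectable, between groups | Detectable, paired change |
|---|---|---|---|---|---|
| 70% | 18 | 17.5% | 179/197 = 91% | 0.69 SD | 0.66 SD |
| 80% | 12 | 20% | 179/191 = 94% | 0.84 SD | 0.81 SD |
| 90% | 6 | 22.5% | 179/185 = 97% | 1.17 SD | 1.15 SD |
| 100% | 0 | 25% | 179/179 = 100% | not estimable | not estimable |

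With complete data, the detectable between-group difference would be 2.80 × √(1/59.75 + 1/179.25) = 0.42 SD, and continuers would supply 179/239 = 75% of pairs.

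**Step 4: sensitivity to the 25%.** If 15% to 40% discontinue (36 to 96 people) and 80% of them stop CGM, about 7 to 19 have paired data.

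**Step 5: the missing-data rule.** Missingness here follows an observed treatment decision, so it is not MCAR, and the stated condition for a complete-case analysis fails for CGM. Conditioning on group could formally satisfy missing at random. With few or no month-6 values among discontinuers, however, the imputation model has little to learn from in that group and must borrow the continuers' relationship. The protocol frames missing data as loss to follow-up, and its Limitations section does not mention this source.

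**The case against.** The best counter-argument is that absence of data is inferred, not stated. The Intervention Algorithm section says only that CGM typically stops, for a funding reason, and Table 1 schedules it at Visit 2. The study does place sensors as a visit procedure at inclusion, so a short sensor wear at month 6 is not excluded. The figures and Multimedia Appendix 2 are not at hand. The between-group and imputation sentences are general and do not name CGM. The authors also restrict one CGM analysis to participants still on CGM, and HbA1c already covers everyone.

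Much of this limits the strength of the claim, and three stronger readings should be resisted:

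- A reader might infer that discontinuers will have no month-6 CGM at all and that the comparison will be empty. That is the limiting case. The protocol's wording allows exceptions, and Table 1 points the other way.
- A reader might infer that no missing-at-random model could recover the discontinuers' mean. That holds only with no observed values. With some, the problem is sparse data and extrapolation, and baseline CGM and 6-month HbA1c could inform the model.
- A reader might infer that discontinuers who still have a sensor are mainly those who resumed prandial insulin, or that all continuers had unchanged treatment. The protocol supports neither.

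The conflict itself remains. No month-6 sensor for discontinuers is described, and the restricted analysis shows that the general CGM-change outcome was not meant to be limited in the same way. CGM metrics are listed outcomes, so the general analysis text covers them.

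**Conclusion.** The concern holds as an internal inconsistency with a practical consequence. Unless discontinuers wear a sensor at month 6, about 60 of 239 participants are expected to form the group of interest and about 18 to 0 of them to have paired CGM. Between 91% and 100% of the pooled pairs would then come from participants kept on prandial insulin.

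This rests on three assumptions: the 70% to 100% range for stopping CGM, complete month-6 CGM in continuers, and the 25% planning value. That value is the share thought to have enough β cell function to stop, not an observed discontinuation rate.

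The defect is confined to the CGM secondary outcomes. The primary outcome, HbA1c, questionnaires and severe hypoglycaemia are unaffected, as is the CGM-predictor analysis insofar as it uses the pre-intervention sensor. It should be fixed before analysis, but it does not threaten the main result.

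**What to change.** First, reconcile Table 1 with the Intervention Algorithm section by stating whether participants who stopped prandial insulin have month-6 CGM data.

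**If they do not:**
- restrict CGM-metric change to participants still on CGM and label it that way;
- remove CGM metrics from the discontinuation-versus-continuation comparison;
- do not impute discontinuers' 6-month CGM values;
- use HbA1c, already scheduled for everyone at Visit 2, as their glycaemic outcome;
- qualify the Visit 2 CGM tick in Table 1.

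**If some do:**
- report the number with paired CGM in each group;
- present CGM change by group, not pooled;
- treat any imputed CGM result as a sensitivity analysis only.

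The cost is wording in the outcome and analysis sections and one table footnote, with no new data. The protocol says formal analysis starts only after follow-up ends, which leaves room for the change to be made before the analysis. The downside is that no claims, or only limited ones, about time in range and time below range can be made for discontinuers.

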### Study Outcomes

We defined the primary study outcome as the proportion of participants in whom prandial insulin is successfully discontinued after the application of the therapeutic algorithm and who remain without prandial insulin at the final visit (6 months).

Secondary outcomes encompass several domains. Glycemic control following therapeutic optimization is evaluated through changes in HbA_1c_ and CGM-derived metrics, including time in range and time below range. Patient-reported outcomes are also assessed by comparing changes from baseline to 6 months after the intervention, including changes in quality of life (using the Diabetes Quality of Life Questionnaire), treatment satisfaction (using the Diabetes Treatment Satisfaction Questionnaire, both status and change versions), medication adherence (measured using the Adherence to Refills and Medications Scale), and physical activity levels (evaluated using the Spanish version of the International Physical Activity Questionnaire).

Safety outcomes include the number of severe hypoglycemic episodes at the final visit 6 months after the intervention compared with the 12-month period before enrollment. The study also examines the predictive value of CGM metrics by analyzing their association with pancreatic reserve and insulin resistance considering both continuous and categorical variables.

Finally, among patients who continue prandial insulin and CGM use for 6 months, the study assesses the impact of CGM on glycemic control (HbA_1c_ and CGM metrics), as well as changes in quality of life, treatment satisfaction, and medication adherence.

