### Study Design and Settings

We designed a nonrandomized pragmatic intervention study targeting people diagnosed with T2DM who were treated with MDI. This before-and-after intervention was designed to assess the real-world applicability of a precision medicine algorithm. Rather than using a control group, this study uses each participant as their own control, comparing clinical outcomes before and after the intervention. The intervention was adapted to be integrated into routine clinical workflows across both primary and specialized care settings.

This study is being conducted within 21 primary health care centers of the Catalan Health Institute (Institut Català de la Salut) in the Lleida health care region (Catalonia, Spain; Multimedia Appendix 1) together with the Department of Endocrinology and Nutrition, University Hospital Arnau de Vilanova, as the reference tertiary center.

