### Sample Size and Statistical Analysis

At the time of the study planning, data from the Lleida health care region had identified 1388 people with T2DM treated with MDI. On the basis of prior clinical experience, approximately 25% of these individuals may have sufficient residual β cell function to discontinue prandial insulin. To estimate this proportion with a 95% CI and a margin of error of –5% to +5%, a sample size of 239 participants was estimated.

The study population will be characterized at baseline with respect to age, BMI, duration of diabetes, presence of chronic diabetes-related complications (microvascular and macrovascular), and cardiovascular risk factors. In addition, in-depth phenotyping will be performed using the homeostatic model assessment of β cell function and homeostatic model assessment of insulin resistance indexes [27] and GADAb measurements.

For the primary outcome, the proportion of participants who discontinue prandial insulin after the application of the diagnostic algorithm and sustain this change over a 6-month follow-up period will be calculated, along with its corresponding 95% CI.

Secondary outcomes will include measures of glycemic control, patient-reported outcomes, and safety outcomes. Glycemic control will be assessed using HbA_1c_ and CGM-derived metrics, including time in range (70‐180 mg/dL), time below range, time above range, mean glucose, and glycemic variability indexes. Patient-reported outcomes will include validated scores for treatment satisfaction, adherence, and quality of life analyzed according to each instrument’s scoring manual. Safety outcomes will include the incidence of severe hypoglycemia.

To evaluate changes over time (eg, from baseline to follow-up visits), paired 2-tailed *t* tests or Wilcoxon signed-rank tests will be used depending on data distribution. Between-group comparisons (eg, discontinuation vs continuation of prandial insulin) will be conducted using Student *t* tests or Mann-Whitney *U* tests as appropriate, as well as using linear mixed-effects models to account for within-subject correlation.

For categorical secondary outcomes, including severe hypoglycemia, comparisons between groups will be performed using chi-square or Fisher exact tests as appropriate. For outcomes measured repeatedly across follow-up visits, analyses will be conducted using linear mixed-effects models.

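### Severe hypoglycemia is compared as a 6-month count against a 12-month count, so an unchanged episode rate reads as a 50% fall

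*Protocol article*

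**What the plan says.** Study Outcomes in the protocol article gives the safety outcome as "the number of severe hypoglycemic episodes at the final visit 6 months after the intervention compared with the 12-month period before enrollment". The data collection schedule uses the same windows. Footnote g of Table 1, on the severe hypoglycemia row, reads "Inclusion visit: last 12 months; final visit: 6 months of study".

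Sample Size and Statistical Analysis returns to the outcome twice. It first says "Safety outcomes will include the incidence of severe hypoglycemia", without defining incidence. It then treats the outcome as categorical: "For categorical secondary outcomes, including severe hypoglycemia, comparisons between groups will be performed using chi-square or Fisher exact tests as appropriate". For change from baseline in general, "paired 2-tailed *t* tests or Wilcoxon signed-rank tests will be used depending on data distribution". Tests are run "with a 2-sided *P* value of <.05 considered statistically significant". The article states no rate per person-time, annualisation, offset or matched 6-month baseline window.

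The design has no control group. Under Study Design and Settings, "this study uses each participant as their own control, comparing clinical outcomes before and after the intervention".

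**The concern.** A count of events grows with the time over which events are counted. The before window is twice as long as the after window, so the raw comparison has a fall built in that owes nothing to treatment. The same holds, very nearly, for the share of participants with at least one episode. The choice of test is a separate matter: a correctly paired test applied to these two numbers would still be biased.

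The direction of the bias is what makes it serious. Severe hypoglycemia is the only outcome the article names under safety. Expected Findings says the study will judge whether prandial insulin can be removed or replaced safely. With no concurrent controls, the before-after contrast carries that message. As defined, it leans towards benefit and can hide a real increase in harm. The Limitations section does not mention it.

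**Working it through.** **Inputs from the article.** Before window 12 months and after window 6 months (Study Outcomes; Table 1 footnote g); planned sample 239; two-sided 5% level; paired t or signed-rank tests for change over time (all Sample Size and Statistical Analysis).

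**Assumed input.** The article gives no rate of severe hypoglycemia, so rates r from 0.05 to 0.5 episodes per patient-year are shown, with lower values considered under the objection.

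**Sample size used.** The 239 reproduces. n0 = 1.96² × 0.25 × 0.75 / 0.05² = 288.1. With the finite population of 1388, 288.1 / (1 + 287.1/1388) = 238.7, rounded up to 239. It was set for the primary proportion, not for this outcome.

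**Step 1: expected counts.** At a constant rate, expected episodes = n × r × time, so after/before = (n × r × 0.5) / (n × r × 1.0) = 0.50 for any r. For example, at r = 0.1, 239 × 0.1 × 1.0 = 23.9 episodes before and 239 × 0.1 × 0.5 = 11.95 after.

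**Step 2: what a real change would look like.**

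| True rate ratio | Apparent ratio of counts | Reads as |
|---|---|---|
| 1.0 | 1.0 × 0.5 = 0.50 | 50% fall |
| 1.5 | 1.5 × 0.5 = 0.75 | 25% fall |
| 2.0 | 2.0 × 0.5 = 1.00 | no change |

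In simulation with r = 0.2 before and a true 50% rise, the raw count still fell in about 90% of runs.

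**Step 3: share with at least one episode.** Under a Poisson model the shares are 1 − exp(−r) before and 1 − exp(−r/2) after.

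| r | Before | After | Spurious fall |
|---|---|---|---|
| 0.05 | 4.9% | 2.5% | 49% |
| 0.2 | 18.1% | 9.5% | 48% |
| 0.5 | 39.3% | 22.1% | 44% |

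**Step 4: false positives from a paired test on raw counts.** Simulation with n = 239, no true change and 2000 runs per setting. Before-counts were Poisson with mean r and after-counts Poisson with mean r/2, either with one common rate or with rates varying between patients (gamma, shape 0.2). The figures are the share of runs with P < .05 by the signed-rank test; the paired t test agrees to within about one percentage point.

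| r | Common rate | Varying rates |
|---|---|---|
| 0.05 | 30% | 28% |
| 0.1 | 52% | 47% |
| 0.2 | 81% | 77% |
| 0.5 | about 99% | about 99% |

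In the subgroup expected to stop prandial insulin (25% of 239, about 60 people), the figure at r = 0.2 is about 25% to 29%.

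**Step 5: after correction.** Dividing each count by its observation time gives an expected rate ratio of 1.0 when nothing changes. The paired t test on annualised counts rejected in 4.4% to 5.7% of the same runs, close to the nominal 5%.

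**The case against.** The strongest reply is that the article does not say raw counts will be tested. Its statistics section speaks of incidence, which can mean events per unit of time, and a full analysis plan may annualise. That reading is possible but not established. The word is undefined, the next reference to the outcome treats it as categorical, and Study Outcomes explicitly names a count over two stated windows. The defect lies in what is stated and is not merely missing detail.

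Several narrower points stand:

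- The only tests tied by name to severe hypoglycemia are the between-group chi-square and Fisher tests. Within the 6-month follow-up these compare equal windows and are unaffected. They do not, however, answer the before-after question that the outcome poses.
- The paired-test sentence covers change over time in general, so the false-positive rates illustrate the natural analysis rather than one expressly assigned to this outcome.
- Those rates depend on the assumed r. With a common rate and n = 239, the signed-rank figure drops to about 13% at 0.02 and 7% at 0.01 per patient-year.
- A McNemar test on any episode, which the article does not name, gives about 42%, 76% and 90% at 0.1, 0.2 and 0.3. With strong clustering between patients (gamma shape 0.1), the last two fall to about 41% and 50%.
- The primary outcome is untouched, and time below range is also a secondary outcome.

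Twelve-month recall might under-count earlier episodes and so offset part of the bias. An unmeasured error in the opposite direction does not correct a known factor of two. None of these points alters the expected halving of the count.

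**Conclusion.** The concern holds. Followed as written, the comparison halves the expected number of episodes when nothing has changed, shows a 50% rise as a 25% fall, and shows a doubling as no change. These figures follow from the stated windows alone, assuming a constant rate within each period and full 6-month follow-up; shorter follow-up would enlarge the spurious fall. For the share with any episode, the artefact is slightly smaller, about 44% to 49% over rates of 0.05 to 0.5 per patient-year.

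How often this would yield a significant result depends on an episode rate that the article does not give: from about 28% at 0.05 to about 99% at 0.5 for a paired test on counts in 239 participants, and less at rarer rates. Because the error favours the intervention on the only named safety outcome of an uncontrolled study, it must be corrected before analysis.

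**What to change.** In Study Outcomes, redefine the outcome as severe hypoglycemic episodes per patient-year, before versus after the intervention. In Sample Size and Statistical Analysis, add a within-person Poisson or negative binomial model with log of each participant's actual observation time as offset, reporting the rate ratio with its 95% CI. State there that incidence means this rate, so that the two sections agree.

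If the share with at least one episode is also reported before and after, use equal windows: the 6 months before the inclusion visit against the 6 study months. Recruitment closed on March 31, 2025, so episode dates can no longer be collected prospectively at that visit and would have to be extracted from records. Where dates cannot be recovered, report the rate ratio only.

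The rate analysis needs only the counts and windows already recorded, and no new visits. It costs one sentence in each section, plus record extraction if the equal-window analysis is wanted. The apparent reduction will be less favourable. The change is still feasible on the article's own timeline, which starts formal analysis only after follow-up and final data collection are complete.
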